## **7.2 Cisgender Female and Transgender Male Patients**

7.2.1 All patients of providers who have the eligible visit types scheduled will be enrolled. We will request for them to complete the eSHxForm before arrival at the clinic or immediately before seeing a provider.

7.2.2 Waiver of informed consent is being requested (see below **Section 12.5.3**) for the eSHxForm and clinical trial procedures. Whereas a waiver of documentation of consent (e.g., oral consent) is being requested for in-depth interviews.

7.2.3 Semi-structured in-depth interviews to evaluate the project (e.g., mainly processes) will occur throughout the project until we obtain feedback from 10-12 patients from each HIV risk level (n=30-36, low, medium, and high). We are not interested in the patients themselves for this portion and will not collect any of their PHI as part of these in-depth interviews.

## **7.3 Clinic staff and other key stakeholders**

7.3.1 Recruitment will be via email, flyers (print and electronic), and word of mouth. Clinic staff will not be recruited nor consented by a direct supervisor. Clinical staff responding to an email or flyer will discuss the study with a research coordinator, who is not a direct supervisor. Recruitment will take place during clinical staff meetings, before scheduled educational sessions, during scheduled work breaks, and other routine gatherings of clinical staff.

7.3.2 A waiver of documentation of consent is being requested for the focus group discussions and in-depth interviews.

7.3.3 Focus group discussions will be held at each clinic during regularly scheduled staff meetings to discuss the project, possible changes to the workflow, and address any concerns.

7.3.4 Semi-structured in-depth interviews to evaluate the project (e.g., mainly processes) will occur throughout the project until we obtain feedback from 10-12 clinic stakeholders. We are not interested in the staff members themselves and will not collect any of their PHI.

## **7.4 Fidelity checks**

7.4.1 A research coordinator will observe the implementation of the study at the clinic and take field notes about the workflow, patients' questions, and providers' and stakeholders' concerns. The field notes will be analyzed every six months and used for cost analyses. Additionally, at every 6-month checks, the proportion of consecutive eligible patients who complete the eSHxForm will be assessed per clinic. If

completion is <75%, then research staff will obtain immediate feedback from clinical staff about barriers to completion and devise a plan to increase completion.

#### 7.4.2 Focus group discussions for process evaluations (every 6 months for 18 months)

Additionally, we will conduct stakeholder virtual focus group discussions (FGD) during standing clinic staff meetings twice yearly. The FGDs will ask the following questions: **R** – How do you suggest we reach more patients?; **A** – Describe how well you felt equipped to deliver the interventions with the training you received? What would be necessary to build skills and confidence in intervention delivery in the future?; **I** – How do you report any suggestions you may have to improve the study procedures and delivery of the interventions?; **M** – What is the likelihood that you would continue with the interventions? What do you think would be needed for other staff to deliver the interventions in the future? We will not address Effectiveness until study end as to avoid interfering with the clinical outcomes.

#### 7.4.3 Findings from the field notes and FGDs will be adopted and guide the adjustment of our study, including optimizing workflow, improving training updates for providers, and addressing concerns from patients, providers, and other stakeholders.

## 8.0 STATISTICAL CONSIDERATIONS

We have rigorous methods to evaluate the interventions and implementation strategy. We will use the RE-AIM framework to guide the statistical plan (**Table 1**). JHU will be responsible for quantitative data analysis and University of Michigan will be responsible for qualitative data analysis.

| Table 1. Intervention and Implementation Quantitative and Qualitative Outcomes using the RE-AIM Framework |                                                                                                                                                                            |                                                                                                            |                       |                                                                                           |
|-----------------------------------------------------------------------------------------------------------|----------------------------------------------------------------------------------------------------------------------------------------------------------------------------|------------------------------------------------------------------------------------------------------------|-----------------------|-------------------------------------------------------------------------------------------|
|                                                                                                           | Intervention Outcomes                                                                                                                                                      | Implementation Strategy Outcomes                                                                           | Level                 | Data Source                                                                               |
| REACH                                                                                                     | Number of patients with an eligible clinic visit who complete electronic screening assessments                                                                             | Number of screening assessments that are completed electronically either via portal or in-clinic on tablet | Patient               | Appointment scheduling log; EHR-programmed data transferred directly into RedCap database |
|                                                                                                           | Number of patients who were excluded                                                                                                                                       |                                                                                                            | Patient and Clinic    | Appointment scheduling log; Observations, field notes                                     |
|                                                                                                           | Number of patients who view the animation                                                                                                                                  |                                                                                                            | Patient               | EHR-programmed data transferred directly into RedCap database                             |
|                                                                                                           | QUALITATIVE: What strategies do you think worked best to capture eligible patients? What could the clinical staff and providers have done better to reach more people?     |                                                                                                            |                       |                                                                                           |
| EFFECTIVENESS                                                                                             | Number of patients who initiate PrEP (primary outcome)                                                                                                                     | Number of providers who document offering of PrEP                                                          | Patient and Providers | EHR chart review                                                                          |
|                                                                                                           |                                                                                                                                                                            | Number of PrEP prescriptions written                                                                       | Providers             | EHR discrete data element                                                                 |
|                                                                                                           | Number of patients who continue PrEP at 3-, 6-, 9- mos                                                                                                                     | Number of PrEP prescriptions written                                                                       | Providers             | EHR discrete data element                                                                 |
|                                                                                                           | Number of patients who are tested for HIV                                                                                                                                  | Number of providers who document offering of HIV test                                                      | Patient and Providers | EHR lab data for HIV testing; EHR chart review                                            |
|                                                                                                           | QUALITATIVE: What surprised you about the outcomes of the training, counseling, clinical care and/or treatment you received? How would you like to see the data presented? |                                                                                                            |                       |                                                                                           |
| ADOPTION                                                                                                  |                                                                                                                                                                            | Number of clinics that use electronic screening assessments                                                | Clinic                | Appointment scheduling log; RedCap database; Stakeholder feedback                         |
|                                                                                                           |                                                                                                                                                                            | Number of clinics that provide tablets to patients                                                         |                       |                                                                                           |
|                                                                                                           |                                                                                                                                                                            | Number of clinics that assist patients to complete electronic screening assessments                        |                       |                                                                                           |
|                                                                                                           | QUALITATIVE: What could the team have done better to reach and recruit more providers? What are your perceptions of the training that was offered?                         |                                                                                                            |                       |                                                                                           |
| IMPLEMENTATION                                                                                            |                                                                                                                                                                            | Number of providers who decline the recommendations included in the alert                                  | Provider              | EHR-programmed data transferred directly into RedCap database                             |
|                                                                                                           |                                                                                                                                                                            | Number of clinics that complete assessments in other EHR locations that are not a part of this project     | Clinic                | EHR chart review
Observations, field notes
Checklists                               |
|                                                                                                           | QUALITATIVE: Do you think the interventions were delivered according to plan? What costs (including time and burden, not just money) need to be considered?                |                                                                                                            |                       |                                                                                           |

|             |                                                                                                                                                                                                        |          |                                                                    |
|-------------|--------------------------------------------------------------------------------------------------------------------------------------------------------------------------------------------------------|----------|--------------------------------------------------------------------|
| MAINTENANCE | Above measures at 6 months after sample size achieved and research staff no longer providing support                                                                                                   | Provider | EHR-programmed data transferred into RedCap database; chart review |
|             |                                                                                                                                                                                                        | Clinic   |                                                                    |
|             | QUALITATIVE: What is the likelihood that you would continue to support this intervention? What do you think would be needed for other women, providers, or staff to find this intervention meaningful? |          |                                                                    |

## 8.1 Primary endpoints

**8.1.1** Intervention: Proportion of PrEP prescription 4 weeks after clinic visit

**8.1.2** Implementation Strategy: Proportion of patients who complete the eSHxForm, number of providers declining automated orders (timeframe: q6 months)

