## PROTOCOL SUMMARY

|                                 |                                                                                                    |
|---------------------------------|----------------------------------------------------------------------------------------------------|
| TITLE:                   | Clinic-based HIV Identification and Prevention Project using Electronic Resources (CHIPPER) |
| PRINCIPAL INVESTIGATORS: | [name] MPH (Administrative), [name] MPH                                      |
| SAMPLE SIZE:             | N=23,492 (Ob/Gyn clinic providers N=42, Patients N=23,400, Staff =50)                              |
| STUDY POPULATION:        | Ob/Gyn providers, patients, and Hopkins University clinic staff                                    |
| ENROLLING SITE:          | Johns Hopkins University Sch of Medicine ObGyn Clinics, Baltimore                                  |
| STUDY DESIGN:            | Hybrid Type II Effectiveness-Implementation Trial                                                  |
| STUDY DURATION:          | 5 years                                                                                            |
| STUDY SCHEMA:            |                                                                                                    |

[figure not shown]

|                            |                                                                                                                                                                         |
|----------------------------|-------------------------------------------------------------------------------------------------------------------------------------------------------------------------|
| PRIMARY OBJECTIVES: | Effectiveness: increase PrEP uptake
Implementation: measure adoption of the protocol                                                                                 |
| PRIMARY ENDPOINTS:  | Effectiveness: PrEP prescription
Implementation: proportion of patients who complete the electronic Gyn history form, number of providers declining automated orders |

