There is no difference between Arms 2 and 3 regarding information and motivation. The difference between these two arms is the provider activity. We are trying to tease apart a clinic-based intervention that targets patients alone (Arm 2) versus both patients and providers (Arm 3). The primary outcome (behavior) is PrEP uptake, and this will be compared based on the Arm the patient is assigned, as is discussed in the data analysis plan. As competing interests (e.g., lack of time) and difficulty assessing the patient's HIV risk consistently have been listed as provider-level barriers to PrEP uptake; and patients do not perceive themselves to be at-risk of HIV, having these two arms will give us a lot of information about how to increase PrEP in women. For instance, Arm 2 will determine whether patients' awareness of their HIV risk will prompt them to ask their provider about PrEP or increase their desire to start PrEP; while Arm 3 will add an additional PrEP facilitator and determine if providers' awareness of their patients' HIV risk level will prompt them to discuss PrEP or increase PrEP uptake by patients.

**Figure 2. Study Schema.** There are two phases in the project. The first is to prepare documents, train staff, enroll providers and clinics. The second includes the clinical trial.

[figure not shown]

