#### Cisgender female patients

- Patients of enrolled providers aged 15-65 years
- Has an Epic visit type that includes one of the following: well-woman exam (annual exam), STI testing, pre-conception counseling, or contraception consult (birth control).

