## 8.5 Quantitative Analyses.

We will examine whether study randomization to the three intervention arms resulted in similar provider and patient groups by comparing patient and provider level demographics with descriptive statistics. Comparison of the primary outcome between arms will be conducted based on provider arm assignment, in accordance with intention to treat. We will use generalized linear mixed-effect models with logistic regression to examine the difference in PrEP uptake (primary outcome) across arms. To account for the relationship among primary outcomes for patients with the same provider, we will specify a random provider effect. In addition, because some patients may return over the study period and be assisted by a different provider than their initial visit, we will specify a random effect for each patient, and assume a joint multivariate normal distribution for these provider and patient random effects. We will adjust these comparisons for any demographic differences

observed between arms. We will examine the primary outcome stratified by race/ethnicity. In exploratory analyses, we will examine whether intervention effects attenuate over time, as providers and patients may become accustomed to the intervention. **Secondary Outcomes:** Similar to our methods for comparing the primary outcome between provider arms, we will also compare the rate of male partner HIV self-test completion (confirmed via text message or phone/video call) with generalized linear mixed-effect models with a provider and patient level random effects. We will use similar methods to compare the HIV test completion rates of male partner and patients who score low-risk. We will consider adjustment for factors that are imbalanced between arms in these analyses. In addition, we will also examine PrEP uptake among low-risk score patients to determine whether providers who are receiving the intervention are being influenced in their behavior more generally, or if the intervention effect is specific only to intervention patients. R (ver 4.1) will be used for analyses.

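### The primary effectiveness endpoint is a PrEP prescription in the summary and 8.1.1 but PrEP initiation in Table 1, and under 8.1.1 a renewal by a current user counts as uptake

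*Protocol*

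**What the plan says.** The protocol describes the primary effectiveness outcome in several places.

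- **Protocol Summary:** "Effectiveness: PrEP prescription". No time window is given.
- **Section 8.1.1:** "Proportion of PrEP prescription 4 weeks after clinic visit". This is the only place with a window.
- **Section 8.0, Table 1, Effectiveness rows:** "Number of patients who initiate PrEP (primary outcome"), as a patient outcome with no window. In the implementation-strategy column the same block has "Number of PrEP prescriptions written", at provider level, from an EHR discrete data element. Continuation is a further outcome: "Number of patients who continue PrEP at 3-, 6-, 9- mos".
- **Section 4:** "The primary outcome (behavior) is PrEP uptake".
- **Section 8.5:** the mixed model is to "examine the difference in PrEP uptake (primary outcome) across arms". Section 8.3 also powers the trial on uptake. None of these sections defines the term.

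On who is analysed, section 5.2 admits "Patients of enrolled providers aged 15-65 years" who have one of the listed visit types. The five patient exclusions in 5.3 concern established prenatal care, other visit types, language, HIV infection and non-completion of the form. Section 4 defines PrEP-eligible by a risk score of 4 to 10. None of these mentions current or past PrEP use.

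**The concern.** A prescription and a start of treatment are different events. A prescription may be written and never started, so the two give different rates. The protocol attaches the primary label to both, with a window for only one, and the analysis section uses a third term that does not decide between them. An analyst who follows the protocol faithfully could report either as primary.

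The second problem belongs to 8.1.1. The objective in 3.1.1 is to increase PrEP uptake. A patient who is already on PrEP, scores medium or high, and has her prescription renewed within four weeks of the visit meets 8.1.1 as written. Her event is not a response to the animation, the risk message or the alert. Counting it raises the rate in every arm and shrinks the contrast between arms.

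**Working it through.** **Which event is primary.** The passages side by side:

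| Place | Event | Window | Role |
|---|---|---|---|
| Summary | prescription | none | primary |
| 8.1.1 | prescription | 4 weeks | primary |
| Table 1 | patient initiates PrEP | none | primary |
| Table 1 | prescriptions written | none | provider-level implementation outcome |
| 4, 8.3, 8.5 | uptake, undefined | none | primary (co-primary in 8.3) |

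Table 1 lists initiation and prescriptions as separate entries with separate roles. The difference from 8.1.1 is therefore hard to read as loose use of synonyms.

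**Effect of counting renewals under 8.1.1.**

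Inputs from 8.3: 1,170 patients in three arms, so 390 per arm; design effect 1 + (28 − 1) × 0.01 = 1.27; uptake 6% against 15%; stated power 80%. The significance level is not stated; two-sided 0.05 is assumed.

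Effective size per arm: 390 / 1.27 = 307.1.

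Power = Φ[(d − 1.96 × se0) / se1], where d is the difference, se0 = √(2p̄(1 − p̄)/n) and se1 = √((p1(1 − p1) + p2(1 − p2))/n).

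*The plan's own case.* p̄ = 0.105, se0 = 0.02474, se1 = 0.02447. (0.09 − 0.04849) / 0.02447 = 1.696, which gives 95.5%. The stated 80% does not reproduce from these inputs. That is a separate matter; 95.5% is used here as the baseline.

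*With current users counted as events.* Let f be the share of medium/high-risk patients already on PrEP. Assume that all of them renew in the window and that 6% and 15% are the rates among the rest. The observed rates are then f + (1 − f) × 0.06 and f + (1 − f) × 0.15. The protocol gives no value for f, so the table shows a range.

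| f (assumed) | Control | Active | Difference | Renewals as share of control events | Power |
|---|---|---|---|---|---|
| 0% | 6.0% | 15.0% | 9.0 points | 0% | 95.5% |
| 1% | 6.9% | 15.9% | 8.9 points | 14% | 93.7% |
| 2% | 7.9% | 16.7% | 8.8 points | 25% | 91.6% |
| 3% | 8.8% | 17.6% | 8.7 points | 34% | 89.4% |
| 6% | 11.6% | 20.1% | 8.5 points | 52% | 82.0% |

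Worked row, f = 2%: 0.02 + 0.98 × 0.06 = 0.0788; 0.02 + 0.98 × 0.15 = 0.167; 0.02 / 0.0788 = 25%.

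Section 8.5 uses logistic regression, so the crude odds ratio matters too. At f = 0 it is (0.15/0.85) / (0.06/0.94) = 2.76. At f = 2% it is (0.167/0.833) / (0.0788/0.9212) = 2.34.

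*If only a third of the 2% renew in the window:* control is 0.0067 + 0.98 × 0.06 = 6.5%, and renewals are 0.0067 / 0.0655 = 10% of control events.

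*If current users are excluded instead, at f = 2%:* n = 390 × 0.98 / 1.27 = 300.9 per arm and power is 95.1%.

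**The case against.** The best defence is that 8.1.1 is the formal endpoint statement and the summary agrees with it. Only one label in a framework table departs from it. The table came through text extraction damaged, and the initiation entry may have been a merged cell spanning the prescription row, so that initiation was to be measured by prescriptions after all. This lowers the severity, but the contradiction remains. Table 1 still names initiation as primary, gives no window, and places prescriptions in another column at another level.

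A new-user filter is often left to the statistical analysis plan, which is not shown and may contain one. That is fair for programming detail. But 8.1.1 and the eligibility criteria together fix a numerator and a denominator that include renewals, and a later plan could correct this only by departing from them.

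The numerical effect is small. Even with 2% current users all renewing, power stays near 92%, above the 80% that 8.3 asks for. This stands.

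Three stronger readings are tempting and are not supported:

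- That Table 1 also counts renewals. A continuing user does not initiate, and the table lists continuation separately. Such patients would remain in its denominator but not its numerator.
- That initiation would be judged by chart reviewers who know the arm. The chart-review source sits in a row shared with provider documentation of offering PrEP, so it may not apply to initiation. Section 8.4 says study personnel and analysts are masked, and nothing says that an abstractor sees the alert.
- That the share of PrEP users who are women, 1-6% in section 2.1, gives the prevalence of current use in these clinics. It is a different quantity and is not used above.

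**Conclusion.** The concern holds in two limited parts. First, the protocol gives the primary label to two different events, with a window for only one of them, and the terms used in sections 4, 8.3 and 8.5 do not settle the choice. This rests on the text alone. Second, under 8.1.1 as written, renewals by current PrEP users count as uptake.

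The second part should not bias the comparison on average, because providers are randomised, although chance imbalance is possible with 14 providers per arm. The expected effect is a higher control rate and modest dilution. At an assumed 2% prevalence with every current user renewing in the window, control reads 7.9% instead of 6%, a quarter of control events are renewals, and power is 91.6% instead of 95.5%. A lower prevalence or partial renewal makes it smaller, and a higher prevalence makes it larger. The protocol gives neither figure.

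A reader might infer that the trial would be underpowered or its result invalid. The figures do not show that. They show a primary endpoint that is not uniquely defined and that, in its formal version, does not quite measure the stated objective.

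**What to change.** Use one definition in the Protocol Summary, 8.1.1 and Table 1: at least one new PrEP prescription in the EHR discrete data within 28 days of the index visit, yes or no per patient, among medium/high-risk patients with no active PrEP prescription at that visit. State that uptake in sections 4, 8.3 and 8.5 means this event. Say which visit is the index visit, since 8.5 expects some patients to return. List initiation separately as a secondary outcome, with its own source and window, and remove the primary label from it in Table 1.

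The cost is protocol wording and one medication-list filter in the Epic data pull. A few current users leave the analysis set. At 2% that is about 8 of 390 per arm (0.02 × 390 = 7.8), and power is then 95.1%, practically unchanged from 95.5%.
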